### **6.2 Expected number of research participants to be included**

The primary objective is to determine the number of patients whose molecular alteration(s), identified via the samples, can lead to the utilization of targeted therapy. For this purpose, we want to be able to evaluate 300 cases over 3 years. Taking into account a technical failure rate of 35% (found in the SAFIR01 and SHIVA trials), 460 cases will need to be evaluated over 3 years. An intermediate statistical analysis will be performed after the first 100 typed cases to verify the failure rate: if the technical failure rate is greater than 40%, the study will be stopped.

As part of the Substantial Modification Request No.4 and in order to increase the numbers in the patient subpopulations for the performance of the analyzes planned as part of the secondary objectives, it is planned to include 100 additional patients during 1 year, for a total of 560 patients.

The total duration for inclusion is therefore 4 years.

The duration of patient follow-up is 3 years.

The total duration of the study is 7 years.

## **VII – RIGHT OF ACCESS TO DATA AND SOURCE DOCUMENTS**

The investigator guarantees, for both himself and all persons involved during the progress of the trial, the confidentiality of all information provided by the Paoli-Calmettes Institute until the publication of the study's results. This confidentiality obligation will not apply to information that the investigator will be required to communicate to patients as part of their participation in the trial or to already published information.

The investigator undertakes not to publish, disclose, or use, in any way, directly or indirectly, scientific or technical information relating to the study.

However, in accordance with article R 5121-13 of the Public Health Code, the center and the investigator may provide study-related information to:

- the Minister of Health.
- public medical health inspectors.
- pharmacy inspectors.
- ASN's Director General and inspectors.

The trial may not be the subject of any written or oral comments without the prior approval of the sponsor; all information communicated or obtained during the trial belongs by right to the sponsor, who can freely dispose of it.

## **VIII – QUALITY CONTROL AND ASSURANCE**

The Paoli-Calmettes Institute (IPC) is the sponsor of this project.

The sponsor is responsible for setting up a quality assurance system as described in institutional procedures so that the trial is performed in accordance with both the protocol and Good Clinical Practices.

The IPC's Department of Clinical Research and Development will coordinate the project and ensure quality control.

## **IX – ETHICAL CONSIDERATIONS**

### **9.1 Regulations**

The clinical trial shall be conducted in accordance with:

- the ethical principles of the revised version of the 1964 Helsinki Declaration.
- the Good Clinical Practice (GCP) decision of November 2006.
- the European Directive (2001/20 / EC) on the conduct of clinical trials.
- the Huriet law (No. 88-1138) of December 20, 1988 relating to the Protection of Persons in Biomedical Research and amended by the Public Health Law (No. 2004-806) of August 9, 2004.
- Law No. 2004-801 of August 6, 2004 relating to the protection of physical persons in connection with the processing of personal data and amending law No. 78-17 of January 6, 1978 pertaining to information technology, databases, and civil liberties.
- Law No. 2011-814 of July 7, 2011 relating to Bioethics.

## **9.2 Ethics Committee**

The promoter agrees to submit the study for prior notice to an Ethics Committee (CPP for Comité de Protection des Personnes). The information to be provided will relate to, on the one hand, the methods and nature of the research and, on the other, the guarantees provided for patients participating in this trial.

## **9.3 Declaration to the competent authorities**

This protocol will be the subject of an authorization application to the ANSM.

## **9.4 Patient informed consent**

Prior to carrying out research involving human subjects, the free, informed, and ongoing consent of the subjects must be obtained after they are informed, by the investigator or his representative, of the objective of the research, the conduct and duration of the study, the benefits, the potential risks and constraints of the trial as well as the nature of the product to be studied and the opinion of the Ethics Committee and authorization from ANSM.

The informed consent form will be dated and signed by both the patient and the investigator (one copy to be archived by the investigator and another given to the patient or his legal representative).

The information and informed consent form intended for the patient must be included in the same document in order to avoid any risk of a dispute regarding the content of the disseminated information.

In the case of trials whose objective is to carry out genomics or proteomics analyses, the information form must specify the type of research that will be carried out and the patient must have the possibility of either accepting or refusing the conservation of their biological samples for scientific research purposes.

## **9.5 Investigators' responsibilities**

Investigators involved in the study agree to conduct the clinical trial in accordance with the protocol that will have been approved by the Ethics Committee and the ANSM. Investigators shall not make any modification to the protocol without the sponsor's permission.

The investigator responsible for the trial at each facility shall:

- provide the sponsor with their curriculum vitae as well as those of their co-investigator.
- identify the members of their team participating in the trial and define their responsibilities.
- start patient recruitment after authorization from the sponsor.
- try to include the required number of patients within the established recruitment period.

It is the responsibility of each investigator to:

- obtain each patient's dated and signed informed consent form before any selection procedure specific to the trial.
- regularly fill out the case report forms (CRFs) for every patient included in the trial and give the Clinical Research Assistant (CRA) direct access to source documents so that the latter can validate the CRF data.

- correct, sign, and date any corrections to the CRF of each patient included in the study.
- notify the sponsor of serious adverse events within the required time limits.
- accept regular visits from CRA and possibly from auditors appointed by the sponsor or inspectors from the supervisory authorities.

All documentation relating to the study (protocol, consent forms, CRFs, investigator files, etc.), as well as original documents (laboratory results, radiology images, consultation reports, clinical examination reports, etc.) should be kept in a safe place and treated as confidential material. The archiving of data will be the responsibility of the investigator in accordance with current legislation. The latter must retain the data as well as a patient identification list for a minimum period of 15 years after the end of the study.

## **9.6 Sponsor's responsibilities**

The sponsor is responsible for:

- acquiring insurance covering civil liabilities in the event of harmful consequences of the research for the persons involved.
- communicating to investigators all information necessary for the proper conduct of the research.
- requesting the approval of the Ethics Committee.
- requesting authorization from the ANSM.
- informing the Directors and Pharmacists of participating health care facilities.
- informing the ANSM of any serious events likely to be due to the research or to its early termination the moment the sponsor has been informed.

The sponsor must archive essential documents on study conduct under conditions ensuring their safety for the minimum period stipulated in the GCPs, i.e. 15 years after the end of the research.

## **X – DATA PROCESSING AND RETENTION OF DOCUMENTS AND DATA RELATING TO RESEARCH**

The Data Management Unit of the Paoli-Calmettes Institute will be responsible for processing the study data, which will remain the property of the Paoli-Calmettes Institute, the research's sponsor.

The data processing software used will be the ENNOV CLINICAL® software.

The Paoli-Calmettes Institute agrees to submit this project to the French Data Protection Agency.

## **XI – CONFIDENTIALITY AND PROPERTIES OF RESEARCH DATA**

The investigators agree, for themselves and all persons involved in the trial's progress, to guarantee the confidentiality of all information provided by the Paoli-Calmettes Institute until the publication of the trial's results. This obligation of confidentiality will not apply to information that the investigator will be required to communicate to patients as part of their participation in the trial or to previously published information.

The investigators agree not to publish, divulge, or use, in any way, directly or indirectly, scientific or technical information relating to the trial.

## **XII – INSURANCE**

The IPC agrees to acquire insurance for research involving human subjects in accordance with the current legislation, via the company SHAM ([name]).

## **XIII – RULES RELATING TO PUBLICATION**

The results of this study are the exclusive property of the Paoli-Calmettes Institute and can be used at their sole discretion. All information resulting from the trial is considered confidential, at least until the appropriate analysis and review by the sponsor and the principal investigator has been completed. Results must be published or presented in collaboration with the sponsor.

All publications, abstracts, or presentations including the results of the trial must be submitted for approval to the sponsor (IPC).

In addition, all communications, manuscripts, or presentations must include a section that mentions both the IPC and UMR 1068 as well as any organizations that contributed financially to the research.

The trial's principal investigator will be the primary signatory (1st or last author).

The investigators will be cited according to the number of patients they have or according to the depth of their involvement in the protocol and/or the pathology. The trial's statistician will be cited third, and a member of the DCRD will also be cited.

Likewise, the publication of the ancillary results (biological study) will include the names of those who carried out the ancillary work as well as the names of all the other persons involved.

## **XV – APPENDICES**

Appendix 1: ECOG performance scale

Appendix 2: Investigations summary

Appendix 3: Validation of preclinical models of therapeutic response in locally advanced or metastatic breast tumors

Appendix 4: Study of circulating tumor DNA

Appendix 5: Study of circulating tumor cells

## **Appendix 1: ECOG (Eastern Cooperative Oncology Group) performance scale**

| ECHELLE | ETAT GENERAL
ECOG-ZUBROD/WHO                                                                                                                           |
|---------|-----------------------------------------------------------------------------------------------------------------------------------------------------------|
| 0       | Fully active, able to carry on all pre-disease performance without restriction.                                                                           |
| 1       | Restricted in physically strenuous activity but ambulatory and able to carry out work of a light or sedentary nature, e.g., light housework, office work. |
| 2       | Ambulatory and capable of all self-care but unable to carry out any work activities; up and about more than 50% of waking hours.                          |
| 3       | Capable of only limited self-care; confined to bed or chair more than 50% of waking hours.                                                                |
| 4       | Completely disabled; cannot carry on any self-care; totally confined to bed or chair.                                                                     |

## **Appendix 2: Investigations summary**

| Samples                                                                                                                                                 |                                                                                                                                                                                                                                                                                                                                                                                                                                                                                                                                                              |
|----------------------------------------------------------------------------------------------------------------------------------------------------------------|--------------------------------------------------------------------------------------------------------------------------------------------------------------------------------------------------------------------------------------------------------------------------------------------------------------------------------------------------------------------------------------------------------------------------------------------------------------------------------------------------------------------------------------------------------------|
| Tumor samples                                                                                                                                           |                                                                                                                                                                                                                                                                                                                                                                                                                                                                                                                                                              |
| 
Biopsy
(Sampling limited to 5 fragments per target and to a total of 10 fragments maximum, all targets combined)
 
or
 
Surgical specimen
 | 
Send to the Pathology Department within 2 hours.
At least 3 fragments, in order of priority:
 
 
- A fragment, after verification of tumor cellularity, to be frozen for the imminent extraction of nucleic acids.
 
- A fragment fixed and embedded in paraffin for complementary immunohistochemical or biological studies.
 
- At least one fragment, after verification of tumor cellularity, to be frozen for use in subsequent molecular studies of proteomics and/or genomics.
 
 |
| Blood samples                                                                                                                                           |                                                                                                                                                                                                                                                                                                                                                                                                                                                                                                                                                              |
| 
5 tubes of 4 ml blood in EDTA, i.e. 20 ml to obtain the genome of normal cells and to perform analyses on circulating tumor DNA.
                        | 
Send to Biological Resource Center within 2 hours.
 
Centrifuge: 800G for 10 minutes at 4°C. Separate:
 
 
- the pellet
 
 
Freeze the dried pellet for nucleic acid extraction.
 
 
- the plasma
 
 
Aliquot in cryotubes and store at -80°C for analyses of circulating tumor DNA.
                                                                                                                                                           |

| Supplementary samples                                                                                             |                                                                                                                                                                                                                                                              |
|--------------------------------------------------------------------------------------------------------------------------|--------------------------------------------------------------------------------------------------------------------------------------------------------------------------------------------------------------------------------------------------------------|
| Tumor samples in the specific case of breast cancer (locally advanced or metastatic) or lung cancer               |                                                                                                                                                                                                                                                              |
| 
Biopsy
 
or
 
Surgical specimen
                                                                         | 
When available, an additional fragment will be transferred, via the Pathology Department, to the Marseille Cancer Research Center (UMR1068) for use in the ancillary project validating predictive preclinical models of therapeutic response.
 |
| Blood samples in the specific case of breast or digestive cancer                                                  |                                                                                                                                                                                                                                                              |
| 
5 tubes of 4 ml in EDTA (20 ml total) for analyses of circulating tumor cells.
                                    | 
Send while still cool to the central reception of the IPC and then to the Marseille Cancer Research Center (UMR1068) for the isolation of circulating tumor cells.
                                                                                    |
| Tumor and blood samples in the event of a relapse (at the discretion of the investigator)                         |                                                                                                                                                                                                                                                              |
| 
Biopsy
(Sampling limited to 5 fragments per target and a maximum of 10 fragments total, all targets combined)
 | 
Send to Pathology Department within 2 hours.
At least 3 fragments, in the following order of priority:
 
 
- A fragment, after verification of tumor cellularity, to be frozen for the imminent
 
     |

|                                                                                |                                                                                                                                                                                                                                                                                                                                                               |
|--------------------------------------------------------------------------------|---------------------------------------------------------------------------------------------------------------------------------------------------------------------------------------------------------------------------------------------------------------------------------------------------------------------------------------------------------------|
| or

Surgical specimen                                                    | 
extraction of nucleic acids.
 
 
- A fragment fixed and embedded in paraffin for complementary immunohistochemical or biological studies.
 
- At least one fragment, after verification of tumor cellularity, to be frozen for use in subsequent molecular studies of proteomics and/or genomics.
 
 |
| 5 tubes of 4 ml in EDTA (20 ml total) for analyses of circulating tumor cells. | 
Send to Biological Resource Center within 2 hours.
 
Centrifuge: 800G for 10 minutes at 4°C.
 
Aliquot in cryotubes and store at -80°C for analyses of circulating tumor DNA.
                                                                                                                                                                |

### **Appendix 3: Validation of preclinical models of therapeutic response in locally advanced or metastatic breast tumors**

Our team has demonstrated the feasibility of establishing patient-derived xenografts from primary breast cancer tumors, which maintain their essential clinical, pathological, and molecular characteristics and allow for the possibility of their use in developing targeted personalized therapies (21). In this project, we aim to establish a bank of breast cancer metastases.

This study aims to validate the feasibility of using these models in vivo and in vitro as predictive models of therapeutic response in patients with metastatic breast cancer.

#### **Establishment of a patient-derived xenograft bank**

The metastatic samples obtained via biopsy or surgery will be dissociated by mechanical and enzymatic methods (digestion by collagenase/hyaluronidase) to generate unicellular suspensions of tumor cells.

These tumor cells are then orthotopically implanted in the fat pads of NSG mice as described by Ginestier et al. 2007 and Charafe-Jauffret et al. 2013 (21, 27). Tumor growth is then monitored bi-weekly, and the xenografted tumor compared to the primary tumor histologically, phenotypically, and molecularly at early or later passages to detect and prevent model drift.

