received the corresponding treatment. For 18 of these, progression-free survival with their treatments lasted more than 1.3 times the length of progression-free survival with previous treatment. The same concept was tested in metastatic breast cancer in the French SAFIR01 trial with promising results. Their analysis of metastatic samples included the search for amplifications in the pan-genome CGH-array and mutations in mTOR pathway (*PI3K*, *PTEN*, *AKT*) genes to see if molecular targets were present that allowed for the referral of the patient to an early trial of targeted therapies. A workable genomic profile was obtained in 64% of patients, 69% of whom had a molecular abnormality of interest for which a targeted drug existed. A targeted personalized treatment was delivered to 43/423 patients with regression or stabilization of the disease of at least 4 months in 13 cases (4). Additional prospective studies are currently underway in France that are testing this concept in patients with all types of metastatic solid tumors: the MOSCATO trial (MOlecular Screening for CANcer Treatment Optimization), sponsored by the Gustave-Roussy Institute; the MOST (My Own Specific Treatment) trial, sponsored by the Léon Bérard Center; and the SHIVA trial, sponsored by the Curie Institute (5). The SHIVA trial plans to evaluate this strategy in a randomized setting for the first time, comparing it to a conventional approach in patients with a molecular abnormality that is potentially targetable by known therapies (imatinib, everolimus, vemurafenib, sorafenib, erlotinib, lapatinib + trastuzumab, dasatinib, tamoxifen, or letrozole). Personalized medicine programs are also underway in several countries: the MD Anderson Cancer Center (6), [name] team in the USA (7), and Toronto in Canada (8). In these studies, typing is performed on a metastatic sample rather than the original tumor due to the appearance of new molecular alterations and resistant clones during tumor progression that may alter therapeutic indications.

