### **2.2 Secondary objectives**

- Define the molecular alterations of advanced malignant solid tumors.
- Compare the molecular portraits of metastatic samples with those of the primary tumor if available (heterogeneity, clonal expansion) and normal cells (somatic or constitutional mutations) from the same patient.
- Determine, for the most frequent diseases (such as breast cancer; lung cancer; gynecological cancers, such as cervical, endometrial, ovarian, and fallopian tube; urological cancer, such as prostate, kidney, and bladder; and digestive cancers, such

as colon, pancreatic, and liver), the relationship between these molecular alterations and the histological and clinical disease characteristics, including progression-free survival and overall survival.

- Perform pan-genomic molecular analysis on metastatic samples with full exome sequencing and transcriptome analysis (expression, fusion transcripts: DNA microarray, RNA-seq).
- Perform an analysis of circulating tumor DNA.
- In the case of breast cancer, validate preclinical models of therapeutic tumor response (xenografts, short-term culture, and organoids).
- In cases of breast and digestive cancer, validate the isolation and characterization of circulating tumor cells.

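### Appendix 3 grows xenografts from metastatic samples but names the primary tumor as the reference for model drift, so disease evolution and graft change are mixed

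*Protocol*

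**What the plan says.** Under *Establishment of a patient-derived xenograft bank*, Appendix 3 describes the starting material: "The metastatic samples obtained via biopsy or surgery will be dissociated by mechanical and enzymatic methods". The resulting cells are implanted in mice. The next step has "the xenografted tumor compared to the primary tumor histologically, phenotypically, and molecularly at early or later passages to detect and prevent model drift".

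Four other places bear on the choice of reference:

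- The opening of Appendix 3 recalls earlier work "establishing patient-derived xenografts from primary breast cancer tumors" and then sets a different aim: "In this project, we aim to establish a bank of breast cancer metastases".
- Section 1.3, describing comparable personalized-medicine studies, says that "typing is performed on a metastatic sample rather than the original tumor due to the appearance of new molecular alterations and resistant clones".
- Section 2.2 makes comparison of metastatic portraits with "those of the primary tumor if available" a separate secondary objective.
- Appendix 3, *Assessment of therapeutic response*, has mutational status assessed in the expanded xenograft and in the patient's tumor sample. It does not call this a drift check and does not extend it to histology, phenotype or the wider molecular profile.

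**The concern.** A drift check asks whether a model still resembles the tissue from which it was made. The reference named here is a different tissue for any graft made from a metastasis. By the protocol's own rationale, the two tissues can differ before any mouse is involved. A graft that copies its metastasis exactly could then differ from the primary, and a graft that has lost metastasis-specific alterations could look closer to it.

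The models go on to be exposed to a panel of nearly 50 drugs, and Appendix 3 wants to know whether they can predict response in patients with metastatic breast cancer. For that use, what matters is fidelity to the sampled metastasis. If the comparison is followed as written, a difference cannot be attributed to the model or to the disease from that comparison alone.

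**Working it through.** The plan attaches no figure, score or threshold to this comparison, so there is nothing to reproduce. The check sets the texts side by side and follows one alteration through the three tissues.

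**1. Source and reference.** Source: metastatic sample (Appendix 3, xenograft bank). Drift reference: primary tumor (same section). The protocol elsewhere treats these as distinct tissues: section 2.2 compares one with the other, Appendix 5 lists them as alternatives, and the opening of Appendix 3 contrasts earlier grafts from primaries with the present bank of metastases.

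**2. What the comparison measures.** For one alteration, write *p*, *m* and *x* for its presence (1) or absence (0) in the primary, the implanted metastatic sample and the graft. Then

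*x* − *p* = (*m* − *p*) + (*x* − *m*).

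The first term is disease evolution and the second is drift. The stated comparison observes only the left-hand side.

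| *p* | *m* | *x* | Graft versus primary | Graft versus source (drift) |
|---|---|---|---|---|
| 0 | 0 | 0 | 0 | 0 |
| 0 | 0 | 1 | 1 | 1 |
| 0 | 1 | 1 | 1 | 0 |
| 0 | 1 | 0 | 0 | −1 |

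The cases with *p* = 1 mirror these. Where *p* = *m*, the two comparisons agree. Where *p* ≠ *m*, they disagree: a retained metastatic alteration shows as a difference (third row), and a lost one shows as agreement (fourth row). Section 1.3 says that alterations with *p* = 0 and *m* = 1 arise. The documents do not say how many, so the size of the mixing cannot be computed.

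**3. When the comparison can be run.** Section 4.2.1 collects the locally advanced tumor or the metastasis. It makes no separate provision for the primary of a patient whose metastasis is sampled, and section 2.2 has the primary only where available. Where it is not, the stated comparison has no reference. The documents give no availability rate.

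**4. What else in the plan observes *x* − *m*.** The mutational-status step in *Assessment of therapeutic response* allows it for mutations. Comparing a later with an early passage gives *x*(late) − *x*(early), in which *m* cancels. That shows change during passaging but not change at first engraftment. No text sets graft against source for histology, phenotype or the wider molecular profile.

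**The case against.** The best defense is that the phrase is loose or translated wording for the tumor of origin. Appendix 3 uses several terms for the reference tissue, and the translation keeps some French words. The team's earlier grafts did come from primaries, so the phrase may have been carried over. This is plausible and cannot be excluded. It does not settle the matter, because elsewhere the protocol uses the term in contrast to metastasis, and a laboratory following the text would look for the primary.

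A second defense is that the damage is small, and most of its parts stand:

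- A reader might infer that true drift cannot be isolated at all. The documents do not support that. Mutational status is assessed in the graft and in the patient's sample, early and later passages could be compared with each other, and the sampled lesion is itself profiled.
- A reader might infer that faithful models will be rejected and drifted ones kept. Appendix 3 contains no drift score, threshold or acceptance rule for xenografts, so no such decision is specified.
- A reader might infer that the check fails for many patients. No figure supports that.
- In locally advanced disease the sampled lesion may be the primary itself. Then *p* = *m* and the stated reference is correct.
- The organoid part of Appendix 3 refers to the initial tumor, which can naturally mean the sampled lesion. No error is shown there.

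**Conclusion.** The point holds in a limited form. For grafts made from metastases, the stated histological, phenotypic and molecular comparison uses a reference that is not the source tissue. It combines primary-to-metastasis evolution with change from source to graft, and it is not available where the primary is not. The mutational-status step repairs this in part, for mutations only.

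The conclusion assumes that the primary tumor means what it means in section 2.2, and that the alterations described in section 1.3 occur in some of the sampled patients. If the phrase was meant as tumor of origin, the intention is sound and the sentence still needs correcting, because it determines what the comparison measures.

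The consequence is confined to an ancillary study, run when an additional fragment is available and serving one secondary objective. The primary objective, the sample size and the interim check on technical failure are unaffected. The correction should be made because it is nearly free, not because the trial's main result is at risk.

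**What to change.** In Appendix 3, *Establishment of a patient-derived xenograft bank*, name as the drift reference the matched lesion from which the graft was made: the locally advanced or metastatic sample taken in the study. State that its CGH-array and NGS profile and its paraffin fragment are used. Use the same term in *Assessment of therapeutic response*, so that both steps plainly refer to one tissue. Keep any comparison with the primary under the heterogeneity objective in section 2.2, where a primary is available.

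The cost is essentially wording. Sections 4.2.1 and 4.4.1 to 4.4.3 already plan the profile and the fixed fragment, and no extra sampling is needed. Two limits remain. The reference is a neighboring fragment of the same lesion, so variation within the lesion is not removed. Section 6.2 also allows for a 35% technical failure rate, so some lesions may lack a usable molecular profile. A sentence saying that the comparison then rests on whatever source material is available, such as the paraffin fragment, would cover this.
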